### The current trial

The overall aim of this RCT is to demonstrate the efficacy of a newly adapted psychotherapy intervention protocol in comparison to treatment as usual (TAU) in the understudied population of physically and sexually abused adolescents and young adults suffering from PTSD. Severity of PTSD symptoms before and after therapy serves as a primary outcome. Secondary goals are to evaluate changes in general psychopathology and comorbidity, such as depression, borderline personality features, and dissociation. Thirdly, the trial will allow for an estimation of the efficacy of TAU in Germany, on which currently no data is available.

Adjunct projects will provide new insights in questions beyond treatment efficacy; electroencephalographic (EEG) parameters are collected in an experiment which aims to find neuronal correlates of threat processing evoked by different categories of emotional words. Preliminary studies could show that anxiety disorders modify the way threatening information is processed [29]. By adapting these studies to the current project, multiple research questions may be answered. Namely, it will be possible to investigate differences in information processing between healthy subjects (control group), traumatized but healthy subjects (trauma control group), and traumatized subjects with PTSD (experimental group). In addition to this, the influence of D-CPT on information processing can be assessed on a psychophysiological level.

On the basis of questionnaires and videotaped sessions, potential predictors of treatment success are analyzed. As there is little research about handling PTSD in adolescents, also important variables influencing therapy outcome, such as treatment adherence, therapist competence, and working alliance, are not well studied [30]. Equally sparse is data about societal costs for the treatment of PTSD and/or mental comorbidities like depression or anxiety disorders (direct costs) as well as PTSD-related loss of productivity (indirect costs). No study has ever investigated the indirect costs resulting from PTSD in adolescents and, so far, no study has analyzed any cost data of PTSD or PTSD-treatment in Germany. Using different questionnaires, these issues are addressed in the D-CPT-project.

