### Outcome measurements

#### ***Primary outcome***

Severity of PTSD is measured at each assessment point using the CAPS-CA [33] (in German [35]). The CAPS-CA is a structured clinical interview which rates frequency and intensity of PTSD symptoms on a scale ranging from 0 (never) to 4 (daily or almost daily) and from 0 (none) to 4 (extreme), respectively. According to the German interview guidelines [35], a symptom is recorded as present if both frequency and intensity are at least rated with 1.

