### Sample size calculation

A type I error of 0.05 and a statistical power of 0.8 were used for sample size calculations. As there exists no effect size estimation for TAU in Germany, we suggest an effect size of d = 0.3. Based on the data reported by Harvey and Taylor [16], an effect size of d = 0.9 was assumed for D-CPT. Thus, two groups of n = 45 patients are required for the trial. No adjustment for drop-out is necessary as last observation carried forward substitution of the major study endpoint will be performed during the intention-to-treat analysis.

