### Statistical analysis

To test the hypothesis that D-CPT is superior to TAU, a confirmatory analysis of the study will be calculated as a *t*-test of post-treatment scores of the CAPS-CA. The critical value of alpha will be set to 0.05. Additional analyses focusing on secondary study endpoints or on generating hypotheses for subsequent studies will be performed on an exploratory basis using up-to-date sophisticated statistical models.

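### The confirmatory t-test on post-treatment CAPS-CA ignores the baseline score taken from every patient, so it gives up precision and cannot correct a chance baseline imbalance

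*Protocol article*

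**What the plan says.** The Statistical analysis section fixes one confirmatory test: "a confirmatory analysis of the study will be calculated as a *t*-test of post-treatment scores of the CAPS-CA". It adds that "The critical value of alpha will be set to 0.05". No baseline covariate and no centre term is named, and all further analyses are classed as exploratory.

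Elsewhere the article shows that the baseline score exists. Under The current trial, "Severity of PTSD symptoms before and after therapy serves as a primary outcome". Under Primary outcome, "Severity of PTSD is measured at each assessment point using the CAPS-CA". The Procedure section lists CAPS-CA among the pre-diagnostic instruments and places randomisation after them. Study centers names three treating clinics.

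The Sample size calculation section gives the design inputs: "A type I error of 0.05 and a statistical power of 0.8 were used for sample size calculations"; for the control arm, "As there exists no effect size estimation for TAU in Germany, we suggest an effect size of d = 0.3"; for the experimental arm, "an effect size of d = 0.9 was assumed for D-CPT"; and hence "two groups of n = 45 patients are required for the trial". It adds nothing for drop-out, because missing endpoints are to be filled by last observation carried forward (LOCF).

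**The concern.** The test uses only the second of two measurements that every patient is planned to have. A baseline value of the outcome itself is usually a useful predictor of the final value, and because it is taken before randomisation, adjusting for it raises no validity problem. Leaving it out has one cause and two visible effects. Variance that baseline could explain stays in the standard error, and a chance difference between arms at baseline carries through to the post-treatment difference in proportion to the baseline-to-post correlation.

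The trial has little slack. Its power sits at the 0.80 target with no allowance for drop-out. The Discussion section itself expects difficulty with participation and completion in this age group, and cites a comparable trial that took 6 years to randomise 61 patients.

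This is a stated choice, not a detail left for an analysis plan. A separate plan would have to overrule the protocol. An adjusted analysis brought in after an imbalance was seen could only be exploratory.

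**Working it through.** **Inputs.** From Sample size calculation: alpha 0.05, power 0.80, d = 0.3 and d = 0.9, 45 per arm. The difference of 0.9 − 0.3 = 0.6 SD is inferred. The article does not write the subtraction, but this reading reproduces its sample size. Sidedness is not stated; two-sided reproduces the figure. The correlation r between baseline and post-treatment CAPS-CA is not in the document and is taken over 0 to 0.7.

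**1. The plan's own figure.** Normal approximation: n = 2(1.96 + 0.842)² / 0.6² = 43.6, so 44 per arm. The exact two-sided t-test gives 44.6, so 45 per arm. One-sided gives 35 or 36 and does not fit. Power of the t-test at 45 per arm is 0.804. The sample size is therefore right for the unadjusted test.

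**2. Power after adjusting for baseline.** ANCOVA reduces the residual SD by √(1 − r²). With a small penalty for estimating the slope, the noncentrality is

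0.6 × √(45/2) / √(1 − r²) / √(1 + 1/86) = 2.830 / √(1 − r²), on 87 degrees of freedom.

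An unadjusted trial of about 45/(1 − r²) per arm would give comparable precision (slope penalty ignored).

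| r (assumed) | Noncentrality | Power at 45 per arm | Comparable unadjusted n per arm |
|---|---|---|---|
| 0 | 2.83 | 0.799 | 45 |
| 0.2 | 2.89 | 0.815 | 46.9 |
| 0.3 | 2.97 | 0.835 | 49.5 |
| 0.5 | 3.27 | 0.898 | 60.0 |
| 0.6 | 3.54 | 0.938 | 70.3 |
| 0.7 | 3.96 | 0.975 | 88.2 |

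Without the slope penalty, power at r = 0.3, 0.5 and 0.6 is 0.839, 0.902 and 0.940.

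**3. Adding centre.** Three centres need two more terms. In the least favourable case (centre explains nothing and allocation is not balanced within centre) the penalty becomes √(1 + 3/84) on 85 degrees of freedom. Power is then 0.790 at r = 0, 0.806 at r = 0.2, 0.826 at r = 0.3, 0.891 at r = 0.5 and 0.933 at r = 0.6. Setting (1 − r²)(1 + 3/84) = 1 gives r² = 3/87, so the full model breaks even in precision at about r = 0.19. With baseline alone, r² = 1/87 and r is about 0.11.

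**4. Chance imbalance.** The SD of the baseline difference between arms is √(2/45) = 0.211 SD, so 95% of allocations fall within ±1.96 × 0.211 = ±0.413 SD. The raw 0.211 is 0.211/0.6 = 35% of the planned effect, but only r times it reaches the unadjusted estimate.

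| r | Shift for an imbalance of 0.211 SD | Shift for 0.413 SD | The latter as share of 0.6 SD | Type I error given 0.413 SD |
|---|---|---|---|---|
| 0.3 | 0.06 SD | 0.12 SD | 21% | 0.08 |
| 0.5 | 0.11 SD | 0.21 SD | 34% | 0.13 |
| 0.7 | 0.15 SD | 0.29 SD | 48% | 0.21 |

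The last column uses the fact that, given a baseline imbalance of b standard errors, the null test statistic is about normal with mean r·b and variance 1 − r². Averaged over all allocations, the type I error is still 0.05.

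**The case against.** The strongest reply is that nothing here is an error. In a randomised trial a t-test of post-treatment scores is unbiased on average and holds its nominal alpha, and the sample size was worked out for exactly that test. Lost power then means only that power could exceed the planned target. All of this stands. In addition, the variance due to chance imbalance is already inside the t-test's standard error, so imbalance and lost power are two views of one loss and must not be added together.

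The gain also depends on an undocumented correlation. Entry requires a PTSD diagnosis on the CAPS-CA itself, which may narrow the baseline range, and about 16 weeks of treatment lie between the two scores. At r = 0.2 the gain from baseline is about one percentage point, and adjustment is not strictly free. That is fair, and is why the range starts at 0. The downside is still small: 0.804 falls to 0.799 with baseline alone, or to 0.790 with centre as well, if neither predicts anything.

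The value of the centre term cannot be quantified from the article, and the case does not rest on it. Nor is the mention of severity before and after therapy a contradiction, since it may only describe when the outcome is measured.

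One feature of the plan points the other way. If the baseline visit counts as an observation for LOCF, a patient who leaves before the assessment at about 8 weeks has the baseline score entered as the endpoint. For such patients a baseline imbalance passes through in full.

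**Conclusion.** The concern holds, as a loss of precision and not as invalidity. The only confirmatory test ignores a pre-randomisation measurement of its own endpoint. At 45 per arm and 0.6 SD, adjusting for baseline would raise power from 0.80 to about 0.83, 0.90 or 0.94 at r = 0.3, 0.5 or 0.6, with a gain of about one point at r = 0.2 and a loss of about half a point at r = 0. It would also largely remove an imbalance effect that, at the edge of its 95% range, could amount to 21% to 48% of the planned effect for r from 0.3 to 0.7.

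The results assume a two-sided test, a 0.6 SD difference, complete data and a linear relation between baseline and outcome. The size of the benefit depends on r, which the document does not give. The change should be made, but the trial remains interpretable without it.

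**What to change.** Define the confirmatory analysis as an ANCOVA of post-treatment CAPS-CA on treatment arm, with baseline CAPS-CA as covariate and centre as a fixed effect, tested two-sided at 0.05. Report the adjusted mean difference with its 95% confidence interval. Keep the unadjusted t-test as a supportive analysis. If a mixed model is adopted for missing endpoints, it should carry the same covariates. Baseline is the essential term; centre is secondary.

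The cost is a sentence in the protocol and analysis plan, with no new data, visits or patients. Because the Trial status section reports 31 of 90 patients recruited and the trial is blinded only at rater level, the change should be a dated amendment made before anyone compares outcomes by arm. The sample size can stay at 45 per arm, with any gained power left as reserve.

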### Safety and ethical issues

The trial has been approved by the Ethics Committee of Catholic University Eichstätt-Ingolstadt and is conducted according to the ICH Guideline for Good Clinical Practice (ICH-GCP [68]). Prior to assessments, all patients are informed about study design and procedures including randomization, probable side effects, and the possibility of ending the participation at any time without disadvantages. Informed consent has to be provided by participating patients and by their parents or guardian if the adolescent is younger than 18 years of age. For safety reasons, suicidal tendencies are constantly observed during assessment and treatment. If necessary, patients will be referred to cooperating clinics. Serious adverse events (SAEs) are continuously monitored and reported through the whole trial. In correspondence with the ICH-GCP, the following incidents are defined as SAEs:

• A physical disease with the risk of permanent impairment and a following medical intervention

• Inpatient somatic hospitalization with a minimum of one overnight stay or prolongation of existing hospitalization

• Inpatient psychiatric hospitalization with a minimum of one overnight stay or prolongation of existing hospitalization (including emergency accommodation/crisis intervention service)

• Intoxication with psychotropic substances (including alcohol) and following medical intervention

• Delinquency with judiciary or police contact

• External aggression to property (statutory offense)

• External aggression to persons (statutory offense)

• Intentional self-harming behavior requiring medical aid

• Attempted suicide

• Re-victimization including all traumatic events according to DSM-IV-TR

In case of a SAE, the responsible therapist or study coordinator reports the event to his/her supervisor and an independent Data and Safety Monitoring Board (DSMB). The decision, whether there is a causal link between treatment and occurrence of SAEs, is taken by the DSMB. If severe safety concerns become apparent to the DSMB, the trial will be stopped.

If an investigator has ethical concerns because of the performance at one of the centers, the coordinating investigator or the co-principal investigator will be informed immediately. The coordinating investigator and the co-principal investigator are authorized to discontinue interventions in a trial center because of insufficient and/or inadequate recruitment, insufficient quality of data, or specific problems unforeseeable in advance which render the continuation of the study impossible at that specific center.

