### Planned interventions

Patients are enrolled either to TAU or D-CPT. Patients in TAU will be advised to look for treatment with other therapists in the respective areas. A detailed instruction to find a psychotherapist via internet will be given to the client by the coordinator of the respective study center. TAU patients will be monitored at the corresponding measurement points planned for D-CPT. After follow-up 1, patients can be enrolled into D-CPT if they wish to do so.

D-CPT is organized into four phases [25]. The treatment begins with a commitment phase comprising 5 sessions in 4 weeks. The aim of this phase is to build a therapeutic alliance and to increase and test the adolescents’ motivation for treatment. Safety plans are developed and anti-suicide contracts are signed. In phase 2, patients learn to tolerate and control intensive trauma-related emotions without acting in a dysfunctional way. For this reason, an emotion regulation training based on DBT-PTSD [27] is applied with 6 sessions in 4 weeks. Phase 3 comprises 15 sessions of CPT, according to Resick et al. [24], administered in high frequency (within 4 weeks); this is the central part of D-CPT. Dysfunctional beliefs related to the traumatic experiences are identified and modified by cognitive restructuring. In the last phase of treatment, developmental tasks specific to adolescence are introduced in 4 sessions during 4 weeks (one weekly session). The goal of this final therapy phase is to minimize the risk of future victimization and/or to prevent the choice of abusive partners. Moreover, the last treatment sessions focus on supporting the patient to complete education and to get an adequate vocational training. In sum, D-CPT comprises 30 sessions with 6 optional sessions for crisis intervention or communication with care givers or other institutions. Table 1 summarizes the treatment design and content. Adherence to D-CPT will be ensured by manualization, continuous local as well as central supervision, and ratings of therapeutic adherence and competence of random samples of videotaped sessions. Therapists are trained within one 4-day and one 2-day workshop. After attending the first workshop, every therapist treats at least one pilot case.

**Table 1 T1:** Overview of D-CPT

**Week**	**Sessions**	**Phase**	**Details**
1–4	5	Commitment	Therapy contract, emergency plan
			Lifeline
			Therapy goals

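### SAE capture is at risk of being unequal between the arms, and the printed SAE definition does not name death

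*Protocol article*

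**What the plan says.** In the protocol article, Safety and ethical issues states the aim: "Serious adverse events (SAEs) are continuously monitored and reported through the whole trial". It adds that "suicidal tendencies are constantly observed during assessment and treatment". For a given event, "the responsible therapist or study coordinator reports the event to his/her supervisor" and to an independent DSMB. The DSMB decides whether treatment caused the event, and the trial stops if it sees severe safety concerns.

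Planned interventions describes the contact in each arm. For the experimental arm: "In sum, D-CPT comprises 30 sessions with 6 optional sessions for crisis intervention" and similar purposes. For the control arm: "Patients in TAU will be advised to look for treatment with other therapists in the respective areas", and "TAU patients will be monitored at the corresponding measurement points planned for D-CPT". Control patients may enter D-CPT after follow-up 1.

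Procedure gives the post-treatment and follow-up assessments to independent raters who do not know the allocation.

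The SAE list is introduced as a definition: "In correspondence with the ICH-GCP, the following incidents are defined as SAEs". Ten items follow. Attempted suicide is one of them; death and completed suicide are not.

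**The concern.** Many of the listed events come to light mainly because the patient tells someone: police contact, aggression, self-harm needing medical aid, re-victimisation, a crisis admission. How often such events are recorded then depends on how often the patient meets someone with a duty to report. In D-CPT that person is the trial therapist, seen at every session. In TAU the treating therapist, if the patient finds one, is outside the trial and has no stated reporting duty.

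Two things are at stake. The DSMB may be unable to tell harm from closer observation when it sets the arms side by side, and events in TAU patients may go unseen, which is a safety matter in itself. The missing item for death is a separate defect in the wording of the definition.

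**Working it through.** **1. Contacts with the trial after randomisation**

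Inputs: the phase sizes 5, 6, 15 and 4 sessions over weeks 1–16 (Table 1), 6 optional sessions (Planned interventions), and assessments at about week 8, post-treatment, 3 months and 6 months (Trial design, Procedure). Baseline is not counted because it precedes randomisation.

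The plan's own total reproduces: 5 + 6 + 15 + 4 = 30. With the optional sessions, 30 + 6 = 36. This is an upper bound, since optional sessions may be used with caregivers or institutions.

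| Period after randomisation | D-CPT | TAU |
|---|---|---|
| Up to and including post-treatment | 30–36 sessions + 2 assessments = 32–38 | 2 assessments |
| Whole trial | 30–36 sessions + 4 assessments = 34–40 | 4 assessments |

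The abstract counts four assessments and omits the one during treatment. On that count every cell loses one, and the gap of 30–36 contacts does not change. The gap arises in the treatment period. TAU patients who enter D-CPT after follow-up 1 gain contacts from then on.

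**2. Who could report**

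- D-CPT: the trial therapist, at each session, and the coordinator.
- TAU: of the two named reporters, only the coordinator. The one coordinator contact described is handing over instructions for finding a therapist. The raters at post-treatment and follow-up have no stated SAE role. The text does not say who conducts the week-8 measurement.

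So the statement that SAEs are monitored continuously stands beside monitoring of TAU at the measurement points, with no described mechanism that joins the two.

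**3. What unequal capture would do (illustration)**

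The document gives no capture rates and no SAE risk, so both are assumed. Let the true risk r be the same in both arms, with capture probabilities c_D in D-CPT and c_T in TAU:

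apparent ratio = (r × c_D) / (r × c_T) = c_D / c_T

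- c_D = 0.9, c_T = 0.7: 0.9 / 0.7 = 1.29
- c_D = 0.9, c_T = 0.5: 0.9 / 0.5 = 1.80
- c_D = 1.0, c_T = 0.9, 0.7 or 0.5: 1.11, 1.43 or 2.00
- equal capture: 1.00, no distortion

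In patients, with the planned 45 per arm and an assumed r of 20%: D-CPT 45 × 0.20 × 0.9 = 8.1 recorded, against TAU 45 × 0.20 × 0.7 = 6.3 or 45 × 0.20 × 0.5 = 4.5, with no true difference.

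**4. Death against the ten items**

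The items cover physical disease with risk of permanent impairment and intervention, somatic admission, psychiatric admission, intoxication with medical intervention, delinquency, aggression to property, aggression to persons, self-harm needing medical aid, attempted suicide, and re-victimisation. A fatal course that includes an overnight stay or medical aid for self-harm or intoxication meets an item on the way. A death with no such prior event, for example a suicide where no aid was reached, is not named. It would count only if staff chose to read it into a neighbouring item.

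**The case against.** **A reporting route is not a detection method.** The reporting sentence says who passes on an event that is already known. How events are elicited is not described for either arm, and a condensed article may leave that to the full protocol. The monitoring statements are not limited to D-CPT. This stands as a limit: differential capture is a risk under the stated route, not a shown fact. It does not remove the point, because the article does fix who reports, and that choice favours the arm with a trial therapist.

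**TAU has sources too.** The coordinator deals with TAU patients, and both arms complete a service-receipt inventory (CSSRI) at baseline, post-treatment and both follow-ups. That is correct, and some TAU events would be recalled. But the inventory is not described as an SAE instrument, and no coordinator contact with TAU patients is described after the initial instructions.

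**No between-arm SAE test is stated.** Also correct: the confirmatory analysis concerns the CAPS-CA only, and no rate-based stopping rule is given. The consequence is therefore for the DSMB's judgement and for any descriptive table by arm.

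**Stronger readings.** A reader might infer that SAE counts are demonstrably biased against D-CPT. The document does not support this: the ratios above come wholly from assumed capture rates. A reader might also infer that therapists or coordinators meet TAU patients at the assessments; Procedure gives the post-treatment and follow-up assessments to blinded raters. Lastly, a reader might infer that the gravest outcomes are not reportable at all. That goes too far, since many fatal or life-threatening courses would meet another item.

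**Conclusion.** The point holds as a risk. Under the stated route, the arms differ by 30–36 contacts with a potential reporter during treatment, and TAU has no described mechanism for continuous monitoring. The likely direction is more recorded SAEs in D-CPT and missed events in TAU. The size cannot be derived from the document; 1.3 to 1.8 is an illustration that rests on equal true rates and assumed capture of 90% against 50–70%.

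The omission of death and completed suicide is a plain gap in a list worded as the definition. It is narrow in scope but needs correcting whatever one thinks of the capture question. Neither part affects the primary efficacy analysis.

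**What to change.** 1. At each existing assessment after randomisation, in both arms, the study coordinator goes through the protocol's SAE list with the patient for the period since the last assessment. The coordinator gives TAU patients their instructions and so already knows the allocation. Keeping the task away from the rater protects blinding.
2. Any SAE summary by arm for the DSMB uses these symmetric reports. An event the patient gives at the checklist counts there whether or not it was already known; otherwise the bias would merely be reversed.
3. Events first learned of in therapy sessions are still reported at once and are tabulated separately by source.
4. Reconcile the statement on continuous monitoring with the monitoring of TAU at measurement points by naming this procedure.
5. Add death from any cause, including suicide, and life-threatening events to the SAE definition.

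The cost is a one-page checklist, a few minutes at visits that already take place, and a short wording change. No visits or staff are added. With 31 of 90 patients recruited when the article was written, 59 were still to enter and could be followed this way from the start.
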